## Abstract

**Introduction:**

HIV self-testing (HIVST) presents a convenient, private approach that removes barriers to providing HIV testing services. The Self-Testing Africa (STAR) Initiative aims to scale up HIVST among priority and undertested populations. HIVST has the potential to help maintain testing services during the social distancing restrictions implemented to prevent the spread of COVID-19. This project evaluates linkage to confirmatory testing and treatment for HIV-positive clients for the STAR South Africa site.

**Methods and analysis:**

This secondary data analysis protocol aims to evaluate different HIVST distribution models from a prospective study implemented during November 2017 and December 2020 by Ezintsha, a subdivision of Wits Reproductive Health and HIV Institute. Routinely collected distribution and self-reported HIVST outcomes data will be deidentified and analysed. The main outcomes of interest are linkage to care and treatment among HIVST users who report a reactive HIVST result. Additionally, we plan to determine sociodemographic factors associated with linkage to care and treatment among HIVST users. Descriptive statistics will be used to describe the variables of interest, and modified Poisson regression with robust variance estimation will be performed to identify factors associated with linkage to care and treatment among HIVST users who report a reactive HIVST result. Risk ratios and 95% CIs for the risk ratios will be reported.

**Ethics and dissemination:**

The study protocol has been approved by the University of Witwatersrand Human Research Ethics Committee. The dissemination plan for the study findings will include presentations to local and international health authorities, international conferences and publications in open access journals.

Strengths and limitations of this studyWe investigate linkage to confirmatory testing and treatment for self-testers who report a positive self-test result.We will conduct secondary analysis of data from a prospective study that included different HIV self-testing distribution models.There is limited generalisability given that participation in self-reporting HIV self-test results is voluntary.To address this limitation, we followed up with as many participants as possible via the different self-reporting platforms.

## Introduction

An estimated 7.02 million South Africans are living with HIV, making the national population level HIV prevalence at 12.7% and 19.1% among those aged 15–49 years.^1^ As part of the National Strategic Plan (NSP) on HIV, sexually transmitted infections and tuberculosis, 2017–2022, South Africa, has put in place various efforts to promote HIV testing services (HTS) in order to stop new HIV infections and to prevent AIDS-related deaths.^1^ South Africa’s 2017–2022 NSP sets a target to reduce the number of new HIV infections to under 100 000 by 2022.^1^. Routine HTS in South Africa largely takes a provider-based approach.^2^ This approach requires that individuals present at an HIV testing location either at the health facility, in the community or in the home. While there have been gains in increasing access to HTS, an HIV testing gap remains largely among men and young people due to existing individual and socioeconomic barriers to accessing routine HTS among these populations. Closing this testing gap through increased access to HIV testing approaches that can provide HTS to these undertested populations will be critical to achieve the Joint United Nations Programme on HIV/AIDS ‘95–95–95’ goals.^3^ However, there are new barriers to facility-based HTS in South Africa and elsewhere due to the implementation of quarantine, social distancing and other restrictions to prevent the spread of COVID-19.^4 5^ HIV self-testing (HIVST) is a relatively new approach that provides an opportunity to reach, test, and diagnose or prevent infection among populations who were previously considered unreachable even during the COVID-19 pandemic due to the ability of people to self-test at home or in the facility while practising social distancing.^6–8^

The World Health Organization (WHO) recommends HIVST as an additional approach to providing HTS that could help with closing this testing gap by increasing access and acceptability for HIV testing.^2^ HIVST presents a private and convenient and confidential approach to providing HTS that removes some of the barriers to routine HTS by allowing people to collect their sample and to receive their results in the privacy of their home without interacting with a healthcare professional.^6^ HIVST also has the potential to reduce costs and to save time for the health delivery system and the end user by triaging out the negative patients.^6^ HIVST kits are already available for purchase over the counter in several countries, including the USA, the UK, France, South Africa and Kenya, and have recently been introduced in the public sector in Malawi, Zambia and Zimbabwe.^9^ Since December 2016, the WHO has provided guidelines to facilitate HIVST inclusion in national policies.^6^ National HIV programmes worldwide have been requested to adapt policy and programme documents, including algorithms and training materials, to fully accommodate HIVST.^6^ Consequently, the number of countries with supportive HIVST policies has grown rapidly to 77, with at least 38 countries currently implementing HIVST.^10^ To support the use of HIVST in South Africa, guidelines for HIVST implementation were issued by the National Department of Health (NDOH) in February 2018.

### Self-Testing Africa (STAR) Initiative in South Africa

Despite the efforts to include HIVST in national policies, the market for HIVST was virtually non-existent in South Africa and other low-income and middle-income countries (LMICs) prior to the implementation of the HIV STAR Initiative.^11^ Key challenges to the development of a healthy HIVST market notably included limited evidence on the public health impact and cost-effectiveness of HIVST, uncertain levels of consumer demand and concerns about potential social harms among others.^11^ In response, Unitaid funded the STAR Initiative to establish evidence for HIVST safety, acceptability, feasibility and scalability. The STAR Initiative seeks to accelerate access to HIVST in LMICs by creating an enabling environment with regard to HIVST policies, generating diverse demand through multiple distribution channels adapted to the needs of priority populations and creating advocacy for additional financing, as well as accelerating market entry for suppliers at affordable and sustainable prices.^11^ The STAR Initiative has three phases, and the collaborators include the WHO, Population Services International and a consortium of partners, including London School of Hygiene and Tropical Medicine, Liverpool School of Tropical Medicine, University College London, Society for Family Health and the Wits Reproductive Health and HIV Institute (Wits RHI) in South Africa.^11^ Phase I of the STAR Initiative was implemented in Malawi, Zambia and Zimbabwe (2015–2017) and demonstrated that HIVST can be used accurately, is widely accepted when offered through community, health facility-based and partner-delivered distribution models,^12 13^ and importantly increases uptake of HIV testing among men, including among male partners of pregnant or postpartum women, adolescents, and vulnerable and key populations that do not otherwise use conventional testing services.^14^ Building on these promising findings, STAR phase II was expanded to three new Southern African countries—South Africa, Swaziland and Lesotho—to introduce and inform HIVST scale-up^15 16^ by establishing sustainable systems for HIVST delivery, linkage to confirmatory HIV testing, prevention and treatment services.^16^ The new countries included in phase II represent three of the worst HIV epidemics in the world. STAR phase III, which was launched in 2020, included Cameroon, India, Indonesia, Mozambique, Nigeria, Tanzania, and Uganda to provide technical support for HIVST introduction and help pave the way for larger investments by the Global Fund for HIVST scale-up.

Wits RHI was one of the implementing partner of the STAR Initiative in South Africa and implemented the project in Gauteng, North West, Mpumalanga and Limpopo provinces of South Africa. Approximately 1.2 million HIVST kits were distributed, primarily targeting testing men, young people and key populations. Under the Wits RHI implemented programme, HIVST was offered if recipients did not know their current HIV status or received an HIV-negative result in the last HIV test taken >3 months ago. HIVST was not offered if the recipient was below the age of 12 or known HIV positive or if there was an identified risk of social harm, such as suicidal thoughts, gender-based violence or coerced testing.

This secondary data analysis protocol aims to evaluate different HIVST distribution models from a prospective HIVST study implemented in South Africa. The main outcomes of interest are linkage to care and treatment among HIVST users who reported a reactive HIVST result by examining the proportion of HIVST recipients who reported a reactive HIVST result and sought HIV confirmatory testing and entry into care among clients who received HIVST kits via the different distribution approaches implemented under the STAR Initiative in South Africa.

## Methods and analysis

### Study design

The study is a secondary analysis of routinely collected programme data from a prospective study aims at evaluating different HIVST distribution models implemented during November 2017 and December 2020 by Ezintsha, a subdivision of Wits RHI (see Data collection section). The different models implemented by Wits RHI are based on the NDOH HIV Self Screening Guidelines and are presented in table 1. Briefly, the models included community-based, public sector facility, key population and private sector targeted distribution. Each model had different channels and implementation strategies.

**Table 1 T1:** HIV self-testing distribution models implemented by Wits RHI/Ezintsha

Model	Modality	Description
Community-based distribution	Hotspots	HIVST was offered to high-risk populations at hotspots through fixed pop-up sites. Hotspots include high foot traffic areas such as busy walkways or shopping centres. After a peer educator provided a demonstration on how to use HIVST kits, clients were provided with a choice to take a kit home or to use it onsite either on their own or with the assistance of the distributor. Clients opting to test onsite were given an opportunity to confirm reactive results. All women and men who indicated having a male partner were offered an HIVST test kit for their partners. 5% of consenting primary recipients of HIVST were telephonically followed up for outcomes of HIVST use, result, linkage to care and uptake of ART. From November 2019, all consenting clients were offered a choice to self-report their outcomes using one of the three mhealth platforms, specifically, WebApp, WhatsApp or on the interactive voice response system.
	Transport hub	The description of this modality is the same as the community-based hotspot modality, with a specific focus on distribution in transport hubs, including taxi ranks and train stations.
	Door-to-door	Within a specific mapped community or geographical location, peer educators and/or trained counsellors move from one household to another and offer HIVST to eligible clients residing there. Clients were offered HIVST with the option of either being directly assisted (in the presence of a healthcare provider) or unassisted. Clients who self-report reactive results were offered the option to confirm their results onsite. All women and men who had male partners were offered oral HIVST tests for their partners. To collect information on outcomes of HIVST use, result, linkage to care and uptake of ART, peer educators went back to the residences of all consenting clients.
	Integrated HTS (mobile)	This modality involved the integration of HIVST into existing mobile HIV testing activities. Clients were offered a choice between HIVST onsite or RDT with a counsellor. HIVST kits were distributed to individual clients after a demonstration of how to use them. Clients who opted for HIVST were only offered onsite testing with the option to confirm a reactive HIVST result immediately. Clients who confirmed reactive were referred to nearby health facilities for ART initiation. To collect information on outcomes of linkage to care and uptake of ART, linkage officers checked ART registers of referral health facilities. Integration of HIVST into mobile HTS did not displace traditional blood-based RDT uptake but provided a screening option of increased yield and efficiency for triaging clients for further managed healthcare.
Key population distribution	Sex worker	This modality was implemented alongside the Wits RHI sex worker programme, which provides various health services to sex workers at static sex worker clinics and at outreach sites. Sex workers were offered up to five HIVST kits to take for their network, which would either be their non-client sexual partners, their clients, other sex workers not accessing HTS or a member of the family or friend considered by the sex worker to be at high risk of HIV. This modality was intended to be a secondary only distribution modality; however, sex workers could use one kit for themselves if they needed to test themselves together with one of their recipients. All consenting sex workers were telephonically followed up to determine the usage, linkage to care and ART initiation status of their networks.
Public sector facility distribution	Outpatient department	Within the hospital outpatient waiting areas, peer educators created awareness and provided information on both traditional RDT and HIVST. Clients were then offered the choice between testing themselves onsite using either a blood or oral-based HIVST test inside a provided cubicle or having RDT with a counsellor. HIVST reactive clients were provided with the opportunity to confirm their results and to be initiated on ART immediately. Offering HIVST alongside traditional rapid testing in the outpatient departments provides clients with not only a choice but also a triage system whereby testers who screen non-reactive using HIVST may exit, allowing counsellors and nurses offering rapid testing enough time to focus on likely reactive testers.
Private sector facility distribution	GP practice and nurse-led clinics	Clients attending health services at GP practices or nurse-led Unjani clinics were offered HIV testing using HIVST during their consultation. After a demonstration was provided by the consulting clinician, clients were offered a private testing space within the facility to test themselves and were asked to self-report their result. Confirmatory testing and ART initiation were available onsite. All clients who self-report a reactive result were offered an HIVST test to take home for their partners.
Private sector distribution	Pharmacy	Pharmacists and pharmacist assistants at private pharmacies offered HIVST to adult clients, 17 and older seeking services that might suggest HIV risk, including emergency contraceptive, treatment for sexually transmitted infections, condoms, lubricants, sexual performance enhancers, etc. After a demonstration is offered, clients can choose to either test onsite on their own or take the kit home. Clients who chose to test onsite were given an opportunity to self-report their result to the pharmacist or the pharmacist assistant. All who self-report a reactive result were offered onsite confirmatory testing when available. All women and men who have male partners were offered oral HIVST tests for their partners. Clients were offered mHealth platforms to self-report on use, result and linkage to care.
	Workplace	This involved distribution of HIVST in formal workplaces with a focus on mining, manufacturing, construction, petroleum, agriculture and security sectors. Employees were offered an HIVST test kit to take home. All female employees were offered an HIVST kit for their male partners. 5% of the sample of primary consenting recipients of HIVST was telephonically followed up to obtain information on HIVST usage, result, linkage to care and ART initiation. Beginning August 2019, clients were also offered mHealth platforms to self-report on use, result and linkage to care.
Secondary-based distribution	Antenatal	After a demonstration and social harm assessment, all first visit antenatal attendees were offered HIVST to take home to support testing their sexual partners. The HIVST modality was not intended to replace facility based RDT testing but support testing of male partners. Women could take HIVST kit for herself to support home disclosure. Consenting women were followed up by telephone or at next visit to acquire information on whether HIVST had been used by partner(s) and for test result and linkage data.
	Index testing	HIVST is offered to newly diagnosed HIV-positive clients (ART clinic) to facilitate partner notification. Telephonic follow-up of HIV-positive index to ascertain index partner uptake of HIVST, linkage of positive sexual partner to confirmative testing and treatment initiation.

GP, general practitioner; HIVSS, HIV self-screening; HTS, HIV testing service; mHealth, mobile health; RDT, rapid diagnostic testing; Wits RHI, Wits Reproductive Health and HIV Institute.

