### Data collection

During HIVST distribution, recipients’ age, gender, HIV testing frequency, as well as partner demographics were collected. Recipients were issued a barcode sticker that accompanies the HIVST kits. Duplicate barcodes were attached to the partner’s HIVST kit(s) when provided. This barcode number was entered onto the participant’s distribution data collection form and was used as the unique identifier for recipients and their associated HIVST kits issued. At distribution, HIVST recipients were also informed of the available options for support with testing, linkage to care as well as self-reported follow-up. Consent was sought from recipients for follow-up through one of the four self-reporting platforms offered on the project: telephonic, interactive voice response (IVR), Progressive WebApp (PWA) or WhatsApp messaging (business version). The different self-reporting platforms were offered to provide participants the ability to choose the option that may work best for them and inform which options will be included in the national HIVST policy to support the scale-up of HIVST and to help collect HIVST use and results data nationally. A standardised follow-up questionnaire was administered to consenting HIV self-testers and collected responses on the following: did you use the test? what was the HIV self-test result? did you request confirmatory testing? did you get confirmatory testing? were you linked to care? were you initiated on antiretorvial therapy (ART)? This set of questions was standard across the four follow-up platforms.

For HIVST recipients preferring follow-up by telephone, up to three telephone calls were conducted by a trained linkage officer at 2, 4 and 6 weeks post-distribution to obtain responses on the aforementioned described set of questions. IVR is an automated telephone system that interacts through short messages and calls with HIVST recipients to confidentially self-report their results. The first automated reminder SMS message to use and self-report HIVST results was sent within 24 hours following distribution. A second short message was sent on day 3 (SMS 2). If reporting had not been done at these two interactions, the IVR system automatically called the participant on day 7 to self-report results. Recipients also had the option to make an inbound call to the platform for support and self-reporting at any time postdistribution.

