PWA is a mobile phone-based tool to support participants through self-testing and eventual confirmatory testing. It is accessible as a mobile site but is also downloadable to a phone, where the full site contents can be cached for offline browsing. Users that selected the web app received an SMS 24 hours following distribution, which provided them with a free URL link to access the PWA for registration on the application. Once subscribed, participants were able to access the website link and to self-report their results.

The Chatbot on a WhatsApp for business platform allowed users to send text and voice messages, make voice and video calls, and share images, documents, user locations and other media. HIVST recipients who selected follow-up and linkage support via the WhatsApp platform received a WhatsApp message 24 hours following distribution to confirm subscription. Once subscribed, participants were able to access the platform, which included terms and conditions, assistance through self-testing process and ultimately self-reporting of their results.

We will merge routinely collected programme distribution and HIVST users’ self-reported data. The survey responses were captured and linked to HIVST recipients’ distribution data via telephone number and barcode onto the project database. Data captured into project database were access controlled and regularly checked for quality, including data reconciliations and a data verification.

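### The main outcome rests on users' own reports, but in three of 11 modalities the kit carrier answers for partner and network testers, so linkage proportions are not comparable across modalities

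*Protocol article*

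**What the plan says.** The protocol article ties the main outcome to the user's own report. The Abstract has "The main outcomes of interest are linkage to care and treatment among HIVST users who report a reactive HIVST result", and the section on the STAR Initiative in South Africa repeats it: "The main outcomes of interest are linkage to care and treatment among HIVST users who reported a reactive HIVST result". Data collection names the respondent, "A standardised follow-up questionnaire was administered to consenting HIV self-testers", with items worded in the second person, and the source for analysis: "We will merge routinely collected programme distribution and HIVST users’ self-reported data".

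Table 1, under Study design, describes something different for three of its 11 modalities:

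- Sex worker: "All consenting sex workers were telephonically followed up to determine the usage, linkage to care and ART initiation status of their networks". The modality is meant for secondary distribution, with up to five kits per sex worker, though "sex workers could use one kit for themselves if they needed to test themselves together with one of their recipients".
- Antenatal: "Consenting women were followed up by telephone or at next visit to acquire information on whether HIVST had been used by partner(s"; the sentence goes on to the test result and linkage. Women could also take a kit for themselves.
- Index testing: "Telephonic follow-up of HIV-positive index to ascertain index partner uptake of HIVST", and then the confirmatory testing and treatment of a positive partner.

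Statistical analysis compares linkage and treatment by modality with a chi-square or Fisher's exact test, tests the proportions against an external value with a binomial test, and fits modified Poisson models. It makes no distinction by who supplied the outcome. Limitations covers voluntary reporting, incomplete data, social desirability and non-response, but not proxy reporting.

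**The concern.** The stated denominator and the described follow-up do not fit each other. Taken literally, the definition leaves the three modalities with almost no users who can be scored, apart from sex workers and antenatal women who tested themselves. If carriers' answers are used instead, the outcome in those modalities is measured by a different instrument from the one that the definition names.

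Two filters then act that do not act on a user who reports directly. The carrier must know that the result was reactive, or the tester is not in the denominator. The carrier must also know that the tester linked, or the tester counts as unlinked. Other modalities use the user's own report, onsite confirmation or, for integrated mobile testing, a check of ART registers. A difference in linkage between modalities could therefore reflect the informant rather than the distribution channel.

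The Discussion says that the findings will show which channels perform best and should be taken into national policy. That is the conclusion at risk.

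**Working it through.** **Step 1. Who answers.** The article gives no linkage, disclosure or sample-size figure, so there is nothing to reproduce. Set side by side, its text gives:

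| Modality | Tester of interest | Informant described | Result listed in the row? |
|---|---|---|---|
| Sex worker | Network member, sometimes the sex worker | Sex worker, by telephone | No |
| Antenatal | Partner, sometimes the woman | Woman, by telephone or at next visit | Yes |
| Index testing | Partner | HIV-positive index client, by telephone | Implied, since linkage is that of a positive partner |

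In the index row the informant is already diagnosed, so every outcome described there is a proxy report.

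**Step 2. Can the identifier separate informants?** Data collection says that partner kits carried a duplicate of the recipient's barcode, and that survey answers were linked by telephone number and barcode. The barcode alone therefore does not show whether an answer came from the carrier or the partner.

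**Step 3. What proxy reporting does to the proportion.** All inputs here are assumptions:

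- L = true linkage among reactive secondary testers
- d1, d0 = probability that the carrier knows the reactive result when the tester did, or did not, link
- s = probability that the carrier knows of the linkage, given that the tester linked and the result is known

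Assuming carriers do not report linkages that did not happen:

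observed linkage = s·L·d1 / (L·d1 + (1−L)·d0)

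This exceeds L only if s > L + (1−L)·d0/d1.

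For L = 0.60, d1 = 0.8, d0 = 0.4, the denominator is 0.48 + 0.16 = 0.64:

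- s = 1.0: 0.48/0.64 = 0.75, bias +15 points
- s = 0.8: 0.384/0.64 = 0.60, no bias
- s = 0.6: 0.288/0.64 = 0.45, bias −15 points

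The break-even is 0.60 + 0.40 × 0.4/0.8 = 0.80, which agrees.

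Other cases at L = 0.60:

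| d1 | d0 | s | Observed | Bias (points) |
|---|---|---|---|---|
| 0.6 | 0.6 | 1.0 | 0.60 | 0 |
| 0.6 | 0.6 | 0.8 | 0.48 | −12 |
| 0.8 | 0.2 | 1.0 | 0.857 | +26 |
| 0.8 | 0.2 | 0.6 | 0.514 | −9 |

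The grid took L = 0.4, 0.6, 0.8; (d1, d0) = (0.6, 0.6), (0.8, 0.6), (0.8, 0.4), (0.8, 0.2); and s = 1.0, 0.8, 0.6. Its extremes are:

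- L = 0.8, d1 = d0 = 0.6, s = 0.6: observed 0.48, bias −32 points
- L = 0.4, d1 = 0.8, d0 = 0.2, s = 1.0: observed 0.32/0.44 = 0.727, bias +33 points

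**Step 4. Effect on the planned comparisons.** Suppose true linkage is 0.60 both in a proxy-reported modality and in a directly reported one measured without error. The true risk ratio is 1. With d1 = 0.8 and d0 = 0.4, the expected apparent ratio is 0.75/0.60 = 1.25 at s = 1.0 and 0.45/0.60 = 0.75 at s = 0.6. For the pooled proportion in the binomial test, if a share w of the reactive users counted is proxy-reported and the directly reported users have the same true linkage, the shift is w times the bias. The article does not give w.

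**The case against.** The strongest reply is that a condensed article need not spell out analysis sets. If the denominator means users' own reports, proxy-reported testers are already outside the main analysis and nothing is biased. Limitations also says that comparing modalities is not the main focus. Part of this stands: the article does not say how proxy answers are handled. But it does fix the definition, the data source, the follow-up by modality and the tests between modalities, and these do not fit together. The Discussion still promises to identify the best channels.

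Several stronger readings are tempting, and the text does not support them:

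- *Secondary testers never report.* Sex workers and antenatal women could test themselves, and nothing bars a partner from the self-report platforms. Direct partner follow-up is not described, which is less than being excluded.
- *Linkage is overstated.* That holds only if disclosure goes with linkage and carriers know of most linkages. Carriers unaware of a clinic visit push the figure down.
- *In the sex worker modality a reactive user is recognised only through linkage, giving 100% by construction.* The row omits the result, but Data collection says that the question set, including the result, was the same on all four platforms, telephone among them. At most this is something to check in the data.
- *Partner kits given out in other modalities without described follow-up are missing outcomes that will be imputed.* The denominator is users who reported a reactive result, and Handling missing data does not say that results for unreported partner kits will be imputed.

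**Conclusion.** The point holds in a limited form. In the sex worker, antenatal and index modalities, the follow-up described makes reactive status and linkage of partner and network testers proxy-reported. This conflicts with the self-report definition of the main outcome and makes those proportions not comparable with directly reported or register-checked modalities. The Limitations section does not name the problem.

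Direction and size are unknown. The illustrative range of about −32 to +33 points rests wholly on assumed disclosure and knowledge rates. It shows that the effect could be large enough to reorder modalities, not that it is. The conclusion also rests on Table 1 being a fair description of the follow-up in these modalities.

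**What to change.** In Statistical analysis:

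1. Classify each result and linkage outcome by informant: own report, observed onsite, register, or proxy.
2. Tabulate proxy-reported secondary users separately: carriers followed up, carriers who knew the result, testers reported reactive, testers reported linked.
3. Show the linkage and ART proportions, the binomial test and the modality risk ratios with and without proxy reports.

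In Limitations, name proxy reporting as a limit on the modality comparison, with direction unknown.

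Showing both sets of results is preferable to removing all secondary users from the main analysis, because the stated aim is to evaluate the distribution models and removal would lose most of what three of them contribute.

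The cost is a few sentences, one extra table and a second run of the models. The results without proxy reports will give little or no estimate for the secondary modalities. The informant flag also assumes that the programme data record who answered; if they do not, that should be stated, and the three modalities reported descriptively without a ranking against the others.
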